## PROTOCOL SYNOPSIS

Protocol Title: A pilot study of IFN- $\gamma$  to treat acute myeloid leukemia (AML) and myelodysplastic syndrome (MDS) that has relapsed after allogeneic hematopoietic stem cell transplantation.

Short title: IFN- $\gamma$  for post-transplant relapsed AML/MDS

Rationale: Allogeneic hematopoietic stem cell transplantation (alloSCT) can cure patients with acute myeloid leukemia (AML) and myelodysplastic syndrome (MDS). However, relapsed AML/MDS is the most significant single cause of treatment failure, and the majority of relapsed patients ultimately succumb. Alloreactive T cells in the donor graft can kill residual leukemia cells, mediating the graft-vs-leukemia (GVL) effect. Consistent with this, recipients of T cell-depleted grafts have higher rates of relapse. GVL is more potent against chronic leukemias than acute myeloblastic diseases, and the higher incidence of relapse in patients with AML/MDS reflects a failure in GVL. [name] laboratory discovered a mechanism to explain the GVL-resistance of myeloblastic leukemias. He reported that chronic phase CML cells are killed by alloreactive T cells even if the leukemia cells cannot respond to IFN- $\gamma$ , whereas acute myeloblastic leukemias require the IFN- $\gamma$  receptor to be optimally susceptible to the GVL effect. Moreover, the administration of exogenous IFN- $\gamma$  could rescue the defective GVL mediated by IFN- $\gamma$  knock out T cells. Other groups have reported clinical data suggesting an important role of IFN- $\gamma$  in GVL. Human leukocyte antigen (HLA) expression was reduced in AML samples from patients who relapsed post-alloSCT, relative to their pretransplant samples. This expression could be restored with in vitro IFN- $\gamma$  treatment. These preclinical and clinical data support our hypothesis that IFN- $\gamma$  will promote GVL in patients with AML/MDS that has relapsed after alloSCT. The central goal of this pilot phase 1 trial will be to explore whether IFN- $\gamma$  in this setting is safe and whether it has the desired biological activities on malignant blasts in vivo. We will test IFN- $\gamma$  in relapsed patients as monotherapy and in conjunction with donor leukocyte infusions (DLI). The clinical and biological information from this study is essential to design a phase II trial with a therapeutic endpoint.

### Objectives:

#### *Primary Objectives:*

- 1) Biological objective: To study whether the standard dose of IFN- $\gamma$  is sufficient to upregulate HLA I, HLA II, ICAM-1, and induce phosphorylated-STAT1 in malignant blasts in vivo in patients who have relapsed after allogeneic stem cell transplantation.
- 2) Feasibility and safety objective: To explore the feasibility and safety of administering IFN- $\gamma$  post alloSCT as monotherapy and combined with DLI in patients who have tolerated IFN- $\gamma$  monotherapy.

#### *Secondary Objectives:*

- 1) Evaluate whether there is a reduction in malignant blast burden coincident with therapy.
- 2) Evaluate whether there is a progression of stable graft-versus-host disease (GVHD) or development of de novo GVHD coincident with therapy.

### Essential eligibility criteria:

- a) Recipients of HLA matched allogeneic hematopoietic stem cell transplant with bone marrow or peripheral blood stem cell graft with relapsed AML or MDS.
- b) At least 0.5% bone marrow myeloblasts, before or after cytoreductive chemotherapy.
- c) no increases in systemic immunosuppressive medications (other than to maintain target blood levels) of >50% in the prior four weeks to treat GVHD,
- d) If active grade I or II acute GVHD, no addition of new systemic immunosuppressive medications for the prior two weeks,
- e) If a systemic corticosteroid is used, the dose should be at or less than 0.5mg/kg/day prednisone or equivalent.

Study design (Figure 1): This is an investigator-initiated pilot phase I study to evaluate the safety and biological effects of IFN- $\gamma$  on adult patients with AML/MDS who relapsed after alloSCT. In stage 1, the safety and biological effect of a fixed-dose of IFN- $\gamma$  (100mcg subcutaneously three times per week) will be evaluated. Bone marrow biopsies will be performed before and no earlier than 48 hours to 1 week after the first dose of IFN- $\gamma$  to assess malignant blasts for an IFN- $\gamma$  response based on predicted upregulation in the expression of HLA-class I, II, ICAM-1, and induction of phosphorylated-STAT1 (p-STAT1) on malignant blasts by flow cytometry. We may also perform single-cell RNAseq on samples pre and post IFN- $\gamma$  treatment. In stage 2, subjects for whom donor leukocytes are available and who have tolerated IFN- $\gamma$  will receive DLI in a dose-escalating manner as is already a clinical standard of care. IFN- $\gamma$  will be continued three times a week for four weeks after the first dose of DLI, followed by once-weekly IFN- $\gamma$  for four weeks. If DLI is not available, the subjects will continue IFN- $\gamma$  for eight more weeks. The patients will be off treatment after a 12 week-course of IFN- $\gamma$  with a repeat bone marrow biopsy at this point. The clinical outcomes will be monitored at six months after the first dose of IFN- $\gamma$  and then the subjects will be off study. Figure 1 summarizes the overall study design.

Cohort 2: As we confirmed the safety of IFN- $\gamma$  monotherapy in the first cohort, we will evaluate a second cohort wherein we will shorten IFN- $\gamma$  monotherapy (stage 1) to 1 week before DLI. In stage 1, we will assess the safety a fixed-dose of IFN- $\gamma$  (100mcg subcutaneously three times per week) for one week. The bone marrow biopsies will be performed before and no earlier than 48 hours to 1 week after the first dose of IFN- $\gamma$  to assess malignant blasts for an IFN- $\gamma$  response. In stage 2, subjects who have tolerated IFN- $\gamma$  will receive DLI in a dose-escalating manner. IFN- $\gamma$  will be continued three times a week for seven weeks after the first dose of DLI, followed by once-weekly IFN- $\gamma$  for four weeks. The patients will be off treatment after a 12 week-course of IFN- $\gamma$  with a repeat bone marrow biopsy at this point. The clinical outcomes will be monitored at six months after the first dose of IFN- $\gamma$  and then the subjects will be off study. Figure 2 summarizes the study design for cohort 2.

Sample size: Our goal is to have at least three patients receive at least one dose of DLI. For example, if the first three patients all complete stage 1 and stage 2, this initial pilot study would be completed with three patients. We estimate enrolling six total patients, but not likely more than nine, as some patients may not be able to complete the study due to the development of rapid disease progression or unavailability of DLI. Based on the nature of the transplant populations at our centers, we estimate accrual will be completed within six months.

For cohort 2, we aim to enroll six patients receiving IFN- $\gamma$  and at least one dose of DLI.

[figure not shown]

**Figure 1. Study Design of Cohort 1:** The figure outlines the scheme of how to administer IFN- $\gamma$  and subsequent donor lymphocyte infusions after enrollment. Biospecimens will also be collected, as shown. BM: bone marrow aspirates, DLI: donor lymphocyte infusion, IFN- $\gamma$ : interferon-gamma, PBMC: peripheral blood mononuclear cells

[figure not shown]

**Figure 2. Study Design of Cohort 2:** The figure outlines the scheme of how to administer IFN- $\gamma$  and subsequent donor lymphocyte infusions after enrollment. Biospecimens will also be collected, as shown. BM: bone marrow aspirates, DLI: donor lymphocyte infusion, IFN- $\gamma$ : interferon-gamma, PBMC: peripheral blood mononuclear cells

## **1. OBJECTIVES**

### **1.1 Primary Objectives**

- 1.1.1 Biological objective: To study whether the standard dose of IFN- $\gamma$  is sufficient to upregulate HLA I, HLA II, ICAM-1, and induce phosphorylated-STAT1 in malignant blasts in vivo in patients who have relapsed after allogeneic stem cell transplantation (alloSCT)
- 1.1.2 Feasibility and safety objective: To explore the feasibility and safety of administering IFN- $\gamma$  monotherapy post alloSCT and combined with DLI in patients who have tolerated IFN- $\gamma$  monotherapy.
- 1.1.3 Primary Endpoints
  - 1.1.3.1 Primary biological endpoint:
    - Upregulation of key targets including HLA-ABC and -DR/DQ, ICAM-1 and generation of phosphorylated STAT1 (pSTAT1) in bone marrow malignant blasts post-IFN- $\gamma$  treatment, measured by the changes in mean florescent intensity and percentage of positive cells by flow cytometry
  - 1.1.3.2 Primary safety endpoints:
    - To evaluate the adverse events of IFN- $\gamma$  in relapsed patients after alloSCT per CTCAE v5.0
    - To evaluate the adverse events of IFN- $\gamma$  in relapsed patients after alloSCT with concurrent use of donor lymphocyte infusion per CTCAE v5.0

### **1.2 Secondary Objectives**

- 1.2.1 Evaluate whether there is a reduction in malignant blast burden coincident with therapy.
- 1.2.2 Evaluate whether there is a progression of stable graft-versus-host disease (GVHD) or development of de novo GVHD coincident with therapy.
- 1.2.3 Secondary Endpoints
  - Reduction of malignant blasts after IFN- $\gamma$  therapy and subsequent DLI
  - Incidence of graft-versus-host disease (GVHD) progression after IFN- $\gamma$  therapy and subsequent DLI
  - Incidence of de novo GVHD after IFN- $\gamma$  therapy and subsequent DLI

## **2. BACKGROUND**

### **2.1 Role of IFN- $\gamma$ Therapy for the Relapse after Allogeneic Stem Cell Transplantation**

AlloSCT is a potentially curative therapy commonly prescribed for patients with moderate- to high-risk acute myeloid leukemia (AML) and myelodysplastic syndrome (MDS). The progeny of

alloreactive  $\alpha\beta$  T cells in the donor graft can attack recipient leukemia cells, thereby mediating the graft-vs-leukemia effect (GVL). However, GVL is not consistently effective, and relapsed disease remains the single most common cause of death after alloSCT. The mechanism of GVL-resistance and sensitivity are heterogeneous dependent on the types of hematologic malignancies. For example, chronic-phase chronic myelogenous leukemia (CP-CML) is exquisitely GVL-sensitive, whereas blast crisis CML (BC-CML) is GVL-resistant, despite sharing common biology. Likewise, AML is relatively GVL-resistant. [name] lab established GVL models against mouse CP-CML (mCP-CML) and BC-CML (mBC-CML) created by the retroviral transfer into bone marrow (BM) cells of disease-defining oncogenes. As is the case in the clinic, mCP-CML is very GVL-sensitive whereas mBC-CML is relatively GVL-resistant. Gene deficient leukemias were created to screen for mechanisms of GVL-resistance. The key finding was that mBC-CML required the expression of the IFN- $\gamma$ R for both CD4 and CD8-mediated GVL. In contrast, STAT1/STAT2-/- mCP-CML, which cannot respond to any type of IFN, was fully GVL-sensitive. Our results suggest that effective GVL against myeloblastic leukemias requires a high magnitude of alloreactive T cell response that generates IFN- $\gamma$  whereas a low level smoldering alloreactive T cell response may be sufficient to control CP-CML. IFN- $\gamma$ R-/- AML created by retrovirus transduction with the MLL-AF9 fusion was also GVL resistant. In subsequent unpublished work, [name] found that infusion of IFN- $\gamma$  can, in part, rescue the defective GVL mediated by IFN- $\gamma$ -/- T cells.

Compelling clinical data support an important role for IFN- $\gamma$ . Several groups have reported a lower rate of AML relapse in patients who have early CMV-reactivation, which results in NK cell- and T cell-derived IFN- $\gamma$  production. HLA class I expression was reduced in AML samples from patients who relapsed post-alloSCT, relative to their pretransplant samples, which was restored with in-vitro IFN- $\gamma$  treatment.

In summary, these preclinical and clinical data support our hypothesis that IFN- $\gamma$  will promote GVL in patients with AML/MDS that has relapsed after alloSCT. The central goal of this pilot phase 1 trial will be to study whether IFN- $\gamma$  is safe and if it has the desired biological activities on AML blasts in vivo. Such information is essential to support a phase II trial with a therapeutic endpoint.

## **2.2 The Rationale of Dose Selection and Clinical Study Design of IFN- $\gamma$ after AlloSCT**

The proposed study is an investigator-sponsored study with a primary objective to study a safe dosing regimen IFN- $\gamma$  that is sufficient to stimulate IFN- $\gamma$  receptors on malignant blasts. Patients who developed relapsed AML or MDS after alloSCT with no active or history of III-IV acute GVHD would be eligible. This pilot study has two stages: 1) Evaluation of safety of fixed-dose of IFN- $\gamma$  (ACTIMMUNE) and 2) Fixed doses of IFN- $\gamma$  with a donor lymphocyte infusion (DLI).

IFN- $\gamma$  (ACTIMMUNE; interferon-gamma-1b) for this clinical trial will be supplied by Horizon Therapeutics USA. ACTIMMUNE is FDA approved to reduce the frequency and severity of serious infections associated with chronic granulomatous disease (CGD) and to delay disease progression in patients with severe, malignant osteopetrosis.

A review of the literature supports the safety of IFN- $\gamma$  administration in humans. In CGD, patients (n=63), interferon-gamma-1b was well tolerated with common adverse events including fever (82%), headache (52%), rash (27%), chills (22%), injection site erythema or tenderness (22%), fatigue (22%), diarrhea (22%), vomiting (21%), nausea (16%), myalgia or arthralgia (12.6%). In the dose titration strategy in healthy volunteers, 40 healthy volunteers were

randomized to receive three-week treatment of interferon-gamma-1b three times a week with either no titration (50 mcg/m^2) or titration dosing (15mcg/m^2 during week 1, 30mcg/m^2, during week 2, and 50mcg/m^2 during week 3). The severity of flu-like symptoms was reduced in the dose titration cohort only at 8 hours but not at a 1-week or 3-week treatment period, suggesting the subjects can develop rapid tolerance to the symptoms associated with interferon-gamma-1b. Adverse events observed in the no-titration cohort included injection site erythema (57%), fever (54%), fatigue (23%), flu-like symptoms (23%), headache (57%), dizziness (57%), myalgia (14.3%), and nausea (17%).

Ten clinical trials are investigating IFN- $\gamma$  in cancer patients with two studies actively recruiting. In a study of soft tissue sarcoma (NCT01957709), eight patients received IFN- $\gamma$  100 mcg/m^2 subcutaneously once a week for four weeks or three times a week for two weeks before the surgery. All patients tolerated IFN- $\gamma$  well with no serious adverse event. The observed adverse events include flu-like symptoms (62.5%), fatigue (62.5%), chills (50%), fever (25%), injection site pain (25%), dry mouth (12.5%), diarrhea (12.5%), and night sweat (12.5%), headache (50%), dizziness (12.5%), body aches (25%), arthralgia (12.5%). The investigators reported increased expression of HLA class I and II on tumor cells biopsied two weeks after IFN- $\gamma$  treatment relative to pretreatment biopsies.

The safety and toxicities of DLIs have been well documented in multiple clinical trials. Cytokine therapies such as IFN- $\alpha$ , IL-2, and IL-15 have also been safely administered in combination with DLIs in patients with relapsed myeloid leukemia post-alloSCT.

In the present trial, we will initiate treatment at 100mcg (almost equal to the dose of 50 mcg/m^2 for an adult) three times a week, with the potential to deescalate the frequency of injection for unacceptable toxicity. To explore whether this dosing regimen is sufficient to activate myeloblasts, we will harvest pre- and post-treatment bone marrow specimens to analyze for IFN- $\gamma$  action (upregulation of HLA class I; HLA class II, ICAM-1 and phosphorylation of STAT1). The primary safety concern is the development of GVHD, which is routinely monitored for all alloSCT patients.

| Flu like symptoms       | 3                         | 0        | 0                   | 0        |
| Injection site reaction | 2                         | 0        | 0                   | 0        |
| Malaise                 | 1                         | 0        | 0                   | 0        |
| Myalgia                 | 1                         | 0        | 0                   | 0        |
| Fatigue                 | 0                         | 0        | 1                   | 0        |
| Sinus tachycardia       | 1                         | 0        | 0                   | 0        |
| Hypotension             | 1                         | 0        | 0                   | 0        |
| Abdominal pain          | 0                         | 0        | 1                   | 0        |
| Diarrhea                | 0                         | 0        | 2                   | 1        |
| Dry skin                | 0                         | 0        | 1                   | 0        |
| Nausea                  | 1                         | 0        | 2                   | 0        |

|                          |   |   |   |   |
|--------------------------|---|---|---|---|
| Vomiting                 | 0 | 0 | 1 | 0 |
| GI other: rectal bleed   | 0 | 0 | 1 | 0 |
| Headache                 | 1 | 0 | 0 | 0 |
| Itchy eyes- intermittent | 1 | 0 | 0 | 0 |

[figure not shown]

### **2.3 Should IFN- $\gamma$ be effective, there will be a meaningful clinical impact**

Over decades of clinical alloSCT, there has been little progress in addressing leukemia relapse outside of donor leukocyte infusions (DLI), which is effective against chronic phase CML, but which has limited efficacy against relapsed acute leukemias and MDS. Up to 50% of post-transplant deaths are secondary to relapse. While there is a GVL effect against AML and ALL, relapse rates are higher than for chronic leukemias. No more than 20% of patients with relapsed AML after alloSCT become long-term survivors, and only a small minority can be successfully rescued by DLI. The magnitude of the relapse problem is reflected in the staging of NCI-funded conferences on relapse post-transplant. Despite efficacy, many patients with transplantable malignancies are not offered an alloSCT. In 2018 nearly 8800 alloSCTs were performed in the US and 32,000 worldwide in 2012, the majority for hematologic malignancies (3000 in the US for AML). Yet, in 2019 within the US alone, there will be an estimated 75,000 diagnoses of potentially transplantable leukemias, including 21,450 and up to 42,000 new cases of AML and MDS, respectively. The decision to refer a patient for alloSCT depends on assessing the degree to which alloSCT reduces the risk of relapse relative to treatment-related morbidity and mortality, chiefly GVHD, and infection. This calculation would change if GVL were more potent. Considering these data, successful approaches for augmenting GVL would have a major public health impact.

### **2.4 Scientific impact of this clinical trial**

This pilot study will not be powered for efficacy, though leukemia/MDS burden will be followed as a secondary endpoint. Nonetheless, because we know that relapsed leukemia/MDS always progresses without intervention, any significant reduction in leukemia/MDS burden with IFN- $\gamma$ , with or without DLI, would be reasonable evidence for efficacy and would support the overall hypothesis underlying the trial. Should we find that IFN- $\gamma$  can be safely administered at a dose and schedule that stimulates myeloblasts in vivo, this would strongly support the development of a multi-center phase II study with a primary efficacy endpoint. Moreover, we will not just measure IFN- $\gamma$  concentrations post-injection but will dose based on evidence of IFN- $\gamma$  action on myeloblasts. We also aim to perform single-cell RNAseq (scRNAseq) on AML cells pre- and post-IFN- $\gamma$  treatment, which has also never been done. RNAseq will allow us to focus on changes in cells with a transcriptome consistent with their having stem cell properties. To conduct ancillary studies, we plan to collect the sequential biospecimens including saliva, peripheral blood, and bone marrow from the subjects. The longer-term goal is to understand which IFN- $\gamma$ -induced changes may sensitize myeloblasts to T cell killing. These studies will synergize with work in [name] lab wherein the same questions are being addressed in murine leukemias, which can be genome-edited and then tested in GVL models. The identification of the key changes could in the future, lead to the development of therapies more narrowly focused than is IFN- $\gamma$ .

## **3. PATIENT SELECTION**

### **3.1 Eligibility Criteria**

- 3.1.1 Ages 18 or older
- 3.1.2 Recipients of allogeneic stem cell transplantation for acute myeloid leukemia or myelodysplastic syndrome from a human leukocyte antigen (HLA) matched donor
- 3.1.3 Relapsed of primary disease, prior to or after salvage treatment with at least 0.5% of blasts in the bone marrow by flow cytometry with a clear leukemia-associated immunophenotype.
- 3.1.4 Performance status KPS score >60% (ECOG 0-2)
- 3.1.5 No increases in systemic immunosuppression in the prior four weeks other than to maintain therapeutic levels
- 3.1.6 No systemic corticosteroid with a dose higher than 0.5mg/kg/day prednisone or equivalent
- 3.1.7 No history of grade IV acute GVHD
- 3.1.8 No new systemic immunosuppressive medications in the prior two weeks initiated due to GVHD
- 3.1.9 Willingness to have bone marrow and peripheral blood collected as per the study protocol
- 3.1.10 Must be able to give informed consent

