### **4.2 Registration**

Patients who meet the eligibility criteria will be consented by the research team. Demographic and clinical data will be collected in the Clinical Trials Management Application (CTMA) system.

External subjects will be registered centrally by the Coordinating Center. External sites must keep a log of subjects who have signed an informed consent document. Each external site must notify the Coordinating Center of subject consent within one business day of the consent. The Coordinating Center will enter the subject and consent date in the internal Clinical Trials Management Application (CTMA) for subject tracking.

External sites must verify subject eligibility prior to submitting screening documents to the Coordinating Center. All eligibility documents must be uploaded to a secure web-based

SharePoint for verification by the Coordinating Center. Relevant screening documents include:

Protocol Registration Form

Copy of the subject signed informed consent form

Eligibility Checklist signed by a First Reviewer and Investigator

All source documents needed to verify eligibility

All results collected per the Schedule of Assessments in Section 7 of the protocol

Source documents supporting stratification factors

As submission of pathology materials for diagnostic review and classification is mandatory, confirmation of tissue availability will be required prior to registration

Coordinating Center supplied source documents, as applicable

All requests for subject registration must be made at least 48 hours prior to the planned start of treatment date. The Coordinating Center will review all submitted documents for accuracy and verify all eligibility criteria are confirmed. The Coordinating Center will notify the external site by email of any discrepancies or requests for additional information, as applicable. A subject will not be registered until all outstanding discrepancies are adequately addressed and eligibility has been confirmed.

Once eligibility is confirmed, the Coordinating Center will register the subject in CTMA. The Coordinating Center will email the subject registration confirmation, including assigned subject ID, to the external site the day of subject registration.

Only eligible subjects will be enrolled. Exceptions to inclusion and exclusion criteria are not permitted. External sites should contact the UPMC HCC Sponsor and Coordinating Center for any questions regarding subject eligibility.

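### GVHD-related eligibility is stated inconsistently in the synopsis, Section 2.2 and Section 3.1, and the first-dose check in Section 6.3.1 relies on an active-grade limit that Section 3 does not state

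*Protocol*

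**What the plan says.** The limits appear in three places in the protocol.

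- **Section 3.1, the formal list.** Item 3.1.7 requires "No history of grade IV acute GVHD". Item 3.1.5 requires "No increases in systemic immunosuppression in the prior four weeks other than to maintain therapeutic levels". Item 3.1.8 bars systemic immunosuppressants newly started because of GVHD in the previous two weeks. Item 3.1.6 caps systemic corticosteroid at 0.5 mg/kg/day prednisone equivalent.
- **Section 2.2, the design rationale.** Patients with relapsed disease "with no active or history of III-IV acute GVHD would be eligible".
- **Synopsis, essential eligibility criteria.** Item (c) bars increases in immunosuppression "of >50% in the prior four weeks to treat GVHD", apart from those made to hold target levels. Item (d) reads "If active grade I or II acute GVHD, no addition of new systemic immunosuppressive medications for the prior two weeks". Item (e) gives the same steroid cap as 3.1.6.

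Three other places depend on these limits. Section 6.3.1 withholds the first dose for findings of GVHD beyond the inclusion criteria. Section 8.1.1.1 reports the incidence of GVHD progression and of de novo GVHD under the primary safety analysis. Section 4.2 says "Exceptions to inclusion and exclusion criteria are not permitted".

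**The concern.** Section 2.2 names the development of GVHD as the primary safety concern. The study has no control group, so the GVHD incidence it reports has to be read against who was admitted. A rule that allows no exceptions needs a single set of criteria, and no passage says which text prevails when they differ.

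Two things are at stake. A patient whom Section 2.2 treats as ineligible can be enrolled and dosed under Section 3. And the check made just before the first dose refers to an active-GVHD limit that the formal list does not contain, so the person making the check has to take one from elsewhere.

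**Working it through.** The protocol gives no figure to reproduce here. The check is a side-by-side reading of the current text.

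| Topic | Synopsis | Section 2.2 | Section 3.1 |
|---|---|---|---|
| Past acute GVHD | Silent | Grade III-IV barred | Grade IV barred |
| Active acute GVHD grade | (d) mentions grade I-II, as a condition | Grade III-IV barred | None stated; 3.1.7 implies a bar on grade IV |
| Increase in immunosuppression, prior 4 weeks | (c) bars more than 50%, for GVHD only | Silent | 3.1.5 bars any, for any reason, except to maintain levels |
| New systemic drug, prior 2 weeks | (d) any reason, but only with active acute grade I-II | Silent | 3.1.8 all patients, but only drugs started because of GVHD |
| Steroid cap | 0.5 mg/kg/day | Silent | 0.5 mg/kg/day (agrees) |

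Test cases, each assumed to meet every other criterion (the percentages are illustrative):

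1. **Past grade III acute GVHD, now resolved.** Eligible under 3.1.7, ineligible under 2.2. The synopsis does not address it.
2. **Active grade III on stable, permitted immunosuppression.** Ineligible under 2.2. In Section 3, items 3.1.5, 3.1.6 and 3.1.8 are met and 3.1.7 does not apply. The bilirubin exclusion (3.2.10) may catch some liver disease, but Appendix A also assigns grade III to gut stages 2-4, and nothing in Section 3 catches those.
3. **A 30% increase to treat GVHD three weeks before treatment.** Passes synopsis (c), since 30% is below 50%. Fails 3.1.5.
4. **A 60% increase for a reason other than GVHD, not to maintain levels.** Passes synopsis (c), which concerns GVHD treatment only. Fails 3.1.5.

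The two-week rule, taken alone, divides patients in both directions. A new drug for a non-GVHD reason in a patient with active grade I disease fails (d) and passes 3.1.8 (although 3.1.5 may catch it if a new drug counts as an increase). A new drug for GVHD in a patient with chronic GVHD only is outside (d) and fails 3.1.8.

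Next, whether a later rule closes the gap in case 2. Section 6.3.1 cannot do so by itself, because it refers back to inclusion criteria that state no active-grade limit. The acute GVHD item in Section 6.7 requires discontinuation for new-onset grade 3 or 4 disease, so grade III already present at entry does not trigger it. Section 6.4.1.3 makes DLI conditional on the absence of active grade II-IV GVHD, which keeps such a patient from DLI while the disease is active, but not from IFN-γ monotherapy.

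**The case against.** The strongest reply is that Section 3 is the formal list, the synopsis is an abridgement and Section 2.2 is background. The coordinating centre verifies the eligibility of external subjects from a checklist and source documents before registering them, and Section 6.2.2 records past and current GVHD and its treatment for every subject. Much of this stands, and it rules out several stronger readings that a reader might infer.

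- **That the population is undefined.** It is inconsistently defined. If Section 3 is applied throughout, there is a working population. What remains is that no order of precedence is stated and that Section 3 lacks the limit Section 6.3.1 needs.
- **That the synopsis limits active disease to grade I-II.** Item (d) is conditional. It says what applies "If active grade I or II acute GVHD" is present and does not exclude higher grades. The explicit bar on active grade III-IV is in Section 2.2 only.
- **That Section 3 admits any active grade.** A patient with active grade IV already has a history of grade IV and fails 3.1.7. The gap is grade III.
- **That every conflict exposes more patients.** On increases in immunosuppression, 3.1.5 is stricter than synopsis (c), so applying Section 3 removes patients. Extra exposure relative to Section 2.2 arises only for grade III, past or active.
- **That one such patient is 17% to 33% of the GVHD denominator.** Those are 1/6 and 1/3, taken over DLI recipients. Section 8.1.1.1 does not restrict GVHD incidence to them; at the 9 patients allowed for in cohort 1 the figure is 1/9 = 11%. A patient with active grade III cannot enter a DLI denominator while the disease is active. The fraction holds for any patient in a small study and does not measure this conflict.
- **That baseline GVHD and recent immunosuppression are the main determinants of the GVHD results.** The protocol does not say so. It lists acute GVHD, at up to 61%, as an expected event of DLI itself.

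Section 6.3.1 can also be read through 3.1.5 to 3.1.8 together, so it is imprecise rather than meaningless.

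**Conclusion.** The inconsistency is real, is in the current text, and should be corrected. It has three parts: Section 2.2 against 3.1.7 on past grade III; Section 2.2 against a list with no stated limit on active grade III, which leaves Section 6.3.1 without a clear referent; and synopsis (c) and (d) against 3.1.5 and 3.1.8 on immunosuppression. The steroid cap agrees and is not part of the problem.

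The size is four kinds of patient whose eligibility changes with the passage applied, besides the differences in the two-week rule. The number of such patients cannot be estimated from the documents. The conclusion assumes that no order of precedence is set outside the protocol. If Section 3 were declared to govern, the immunosuppression conflict would be settled in practice, but the mismatch with the stated rationale on grade III and the gap behind Section 6.3.1 would remain.

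**What to change.** Before further enrolment, reconcile the passages into one list in Section 3 that covers three items explicitly: acute GVHD history by grade, active GVHD grade at entry, and permitted changes in immunosuppression, including to whom and to which drugs the two-week rule applies. Make the synopsis, Section 2.2, Section 6.3.1 and the eligibility checklist consistent with that list, and have Section 6.3.1 cite the item numbers it relies on. Which limits stand is for the sponsor's clinicians; no view is taken here.

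The cost is a protocol amendment and a checklist update, with possibly slightly slower accrual if the stricter text is kept.
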